### Primary outcome

2.8

#### Muscle fiber size

2.8.1

Muscle fiber size, measured as muscle fiber cross-sectional area (CSA) represents the primary muscle cellular outcome. Muscle fiber CSA will be measured using immunohistochemistry in cross-sections of muscle biopsies. Briefly, transverse serial sections of the muscle biopsy (8 μm thick) will be cut using a cryostat microtome at −22°C and mounted on glass slides. Serial cross-sections will be immunohistochemically stained for fiber types (type I, type IIa, and IIx) for CSA measure. Muscle fiber CSA will be measured for the different phenotypes separately. Assessors will be blinded to each participant's allocation.

### Secondary outcomes

2.9

#### Regulators of muscle fiber size

2.9.1

Secondary muscle cellular outcomes reflecting regulators of muscle fiber size are

1.number of myonuclei per muscle fiber,2.number of SCs per muscle fiber,3.proteins involved in muscle protein degradation (muscle breakdown), and4.regulators of muscle protein synthesis (local growth factors).

Muscle fiber myonuclear and SC content per muscle fiber will be measured using immunohistochemistry in cross-sections of muscle biopsies as previously described. Myonuclei- and SCs content per muscle fiber will be assessed for the different phenotypes separately (type I, type IIa and IIx). Regulators of muscle fiber size, that is proteins involved in muscle protein synthesis and protein degradation will be measured using Western blot analysis in muscle homogenate. See Table 1 for details.

#### Regulators of muscle fiber function, cellular stress, and mitochondrial function

2.9.2

Proteins involved in protection against cellular stress (Heat Shock proteins: Hsp 27, αB-crystalline, Hsp 60, and Hsp 70), as well as enzymes involved in mitochondrial function (CS, Cox 4, and HAD) will be assessed in muscle homogenate using Western blot analysis. In addition, mitochondrial structure will be studied in cross-sections and whole fiber preparations of muscle biopsies using immunohistochemistry.

#### Myokines with potential antitumor effects

2.9.3

Exploratory analyses on the effects of the RT on the expression levels of myokines, previously proposed to have an antitumor effect, will be conducted. Relevant targets, including, but not limited to, IL-6, IL-15, SPARC, and TWEAK will be evaluated on the mRNA level by real-time PCR analyses (RNA extracted from biopsies) and protein level by Western blot and enzyme-linked immunosorbent assays (ELISA) (muscle and blood samples). Blood samples will be obtained by venipuncture and participants are asked to avoid smoking and alcohol and not to engage in any strenuous physical activity 24 hours before the blood sample. IL-6, IL-8, IL-10, IL-1β, IFN-γ, TNF-α, TNF1R will be measured using ELISA based methods. Frozen sera will be saved for further analyses that can be included later.

#### Muscle strength 

2.9.4

Maximal upper- and lower- extremity muscle strength will be measured as 1 RM in seated chest-press and seated single-leg press. To secure the validity of the 1 RM tests, all participants will undertake a 2-week familiarization period prior to these assessments (both participants in the intervention group as well as participants allocated to the control group).

#### Cardiorespiratory fitness

2.9.5

Cardiorespiratory fitness will be measured as maximal oxygen uptake during maximal walking/running until exhaustion on a treadmill using a modified Balke-protocol^[29]^ starting at 4 km/hour with an incline of 2%. The inclination increases with 1% every minute until reaching 12%, from which the speed increases 0.5 km/hour per minute until exhaustion. Oxygen consumption and minute ventilation will be measured continuously using an oxygen analyzer (Vmax Encore system, Carefusion, CA). Heart rate will be measured using a heart rate monitor (Polar RS400, Kempele, Finland) and self-perceived exertion will be recorded using a standardized Borg-scale.^[28]^

### Additional outcome measures

2.10

#### Body composition

2.10.1

Fat-free mass and fat mass will be measured with air displacement plethysmography (Bod Pod, Life Measurement System Inc., Concord, CA), and bioelectrical impedance analysis (BIA, TANITA BC-420MA, Tanita Corporation, Japan). Bodyweight is measured using BIA and body height is measured with a stadiometer, body mass index (BMI: weight/(height^2^)) is then calculated.

#### Biomarkers of oxygen transportation, stress, inflammation, metabolic outcomes, and muscle damage

2.10.2

Blood samples will be obtained as described earlier and analyzed for levels of hemoglobin, serum-cortisol, long-term average blood glucose (hemoglobin A1c [HbA1c]), blood lipids, C-reactive protein (CRP), and creatine kinase-myocardial band (CK-MB) using standardized clinical measures.

#### Sociodemographic, lifestyle, quality of life, and fatigue

2.10.3

Age, partnership, number and age of children living at home, education, income, work and sick leave will be assessed using a study-specific questionnaire. Dietary habits, alcohol consumption, tobacco use, motivation, self-efficacy, and barriers to exercise are self-reported using a study-specific questionnaire. The EORTC QLQ-C30^[30]^ and diagnosis-specific modules (QLQ-BR25 for breast cancer) will be used to assess health-related quality of life. Cancer-related fatigue will be assessed using the MFI.^[31]^

#### Physical activity level

2.10.4

Physical activity level will be assessed by SenseWear Armband (SWA) Mini (BodyMedia Inc., Pittsburgh, PA). All participants will be instructed to wear the SWA for 7 consecutive days. Only valid days with at least 80% wearing time will be included in the analyses. SWA data will be downloaded and analyzed with software developed by the manufacturer (SenseWear Professional Research Software Version 8.1, BodyMedia Inc., Pittsburgh, PA). During this week, participants will self-report their physical activity level (time spent, types of activity, and its intensity), time spent sleeping, time spent in sedentary behaviors (sitting, lying down during waking hours), use of medications for nausea or pain, and potential sick leave or reduced work capacity in logbooks.

#### Disease and treatment

2.10.5

Information about type and dose of oncological treatment, stage of disease, co-morbidity, central catheter (including type, insertion/removal date, and complications) and treatment side effects will be collected from medical records. Chemotherapy treatment completion rates will be calculated as described by Longo et al.^[32]^

#### Adverse events

2.10.6

Adverse events caused by the exercise are registered by the coaches. Grade 1 (e.g., muscle strain) means that the participant has to terminate the ongoing specific exercise but can continue with the exercise session. Grade 2 (e.g., fall in blood pressure) means that the participant must terminate the exercise session. Any severe adverse events (e.g., fracture) are reported directly to the PI and managed by healthcare. Adverse events from muscle biopsy procedure will also be registered.

### Statistical analyses

2.11

Data will be analyzed according to the intention-to-treat principle. Analyses will include standard descriptive statistics, *t* tests, correlation, regression and two-way repeated-measures ANOVA or the comparable nonparametric test as necessary to examine differences between and within groups, at T0, T1, and T2. In addition, a per-protocol analysis, that is, adherence to the protocol, will be conducted. Should imbalances in important variables be detected, sensitivity analyses will also be added including these as covariates in the model. All data will be cleaned and quality-checked before analysis.

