### Study design

2.1

This study is a two-armed randomized controlled trial with follow-up at 6 months (Fig. 1). Data will be collected before the first cycle of chemotherapy (T0), after chemotherapy (T1), and 6 months later (T2). The primary outcome for this study is muscle fiber size. Secondary outcomes are: regulators of muscle fiber size and function, indicators of cellular stress and mitochondrial function, myokines with potential antitumor effects, muscle strength, and cardiorespiratory fitness. All outcomes are listed in Table 1.

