### Sample size

2.3

The power calculation is based on results from strength training effects in prostate cancer patients on androgen deprivation therapy, the Physical Exercise and Prostate Cancer trial (PEPC trial).^[10]^ With a similar effect on muscle fiber size (+898 ± 840 μm^2^), we need 10 participants in each group to get a statistical power of 80% in the present study, to further enhance the power up to 95%, we need 16 participants in each group. Consequently, 50 participants (25 in each arm) will be recruited to account for drop-outs during the intervention. The power calculation is based on the PEPC trial^[10]^ but findings from the study by Mijwel and colleagues^[13]^ strongly support similar expectations in breast cancer patients on chemotherapy.

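### Repeated-measures ANOVA over T0, T1 and T2, used without imputation, drops anyone missing a visit and so fits poorly with the stated intention-to-treat analysis

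*Protocol article*

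**What the plan says.** The analysis principle in section 2.11 (Statistical analyses) of the Protocol article is plain: "Data will be analyzed according to the intention-to-treat principle". The same section then lists descriptive statistics, t tests and correlation, followed by "regression and two-way repeated-measures ANOVA or the comparable nonparametric test as necessary to examine differences between and within groups, at T0, T1, and T2". The ANOVA, or its nonparametric counterpart, is the only method listed that is by its nature longitudinal. No method in the list is tied to the primary outcome, muscle fiber CSA. A second analysis set is added: "In addition, a per-protocol analysis, that is, adherence to the protocol, will be conducted".

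Biopsies are scheduled at three visits (section 2.1 and Table 1), the last of them six months after the end of chemotherapy. Section 2.3 (Sample size) foresees losses: "50 participants (25 in each arm) will be recruited to account for drop-outs during the intervention". It gives no expected drop-out rate.

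**The concern.** Classical two-way repeated-measures ANOVA works on complete rows. Unless missing values are imputed, a participant with one missing visit is removed from the whole analysis, including from time points at which she was measured. Here the visit furthest from the intervention is a third muscle biopsy, six months after treatment. Someone who gave the T0 and T1 biopsies but not the T2 biopsy has supplied everything needed to estimate the effect of training during chemotherapy, which is what hypothesis 2 in the Introduction is about. The ANOVA would still discard her.

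That sits badly with an intention-to-treat promise in a trial that has enlarged its sample because it expects losses. Two things are at stake. One is power, because observed T1 data go unused. The other is bias in the T1 comparison, if those who skip T2 differ at T1 and do so differently in the two arms.

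**Working it through.** **Inputs from section 2.3.** Planning effect 898 μm² with SD 840 μm²; 10 per group stated for 80% power and 16 per group for 95%; 25 per arm recruited. Alpha and sidedness are not stated; I assume 0.05, two-sided.

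**The plan's own figures.** Taking 840 as the common SD, d = 898/840 = 1.07. A two-sample t test then needs 15 per group for 80% power and 24 for 95%, and has power 0.62 with 10 and 0.83 with 16. The stated 10 and 16 are therefore not reproduced as a between-group comparison. That is a separate matter. Here I use the stated 16 only to read off the allowance for losses, and d only as a scale for power.

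**Implied allowance.** 1 − 16/25 = 0.36. Up to 36% per arm could be lost before the stated need of 16 is breached.

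**Power.** For a two-sample t test with n per arm, the noncentrality is d × √(n/2) on 2n − 2 degrees of freedom. The documents give no attendance figures, so this is a range:

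| n per arm analysed | Power |
|---|---|
| 25 | 0.96 |
| 20 | 0.91 |
| 19 | 0.89 |
| 18 | 0.88 |
| 17 | 0.86 |
| 16 | 0.83 |

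As an example, assume 6 of 25 per arm have no T1 biopsy and 2 more have T1 but not T2. Then 25 − 6 = 19 per arm can inform the T1 contrast, but only 19 − 2 = 17 have complete profiles. Noncentrality falls from 1.069 × √9.5 = 3.29 to 1.069 × √8.5 = 3.12, and power from 0.89 to 0.86. This loss comes from the method, not from the missing biopsies.

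**Bias.** An illustrative simulation assumed:
- no true effect, and 25 per arm;
- SD 840 at each visit and correlation 0.5 between visits, so the SD of change is 840 × √(2 × (1 − 0.5)) = 840;
- T0 and T1 observed for everyone;
- about a quarter missing at T2, at random in the control arm, and in the training arm with strongly higher probability when the T1 value is low.

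| T1 between-group difference in change from T0 | Mean, μm² |
|---|---|
| All participants with T1 data | about 0 |
| Three-visit completers only | about +140 |
| Three-visit completers, loss completely at random | about 0 |

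The +140 is 140/898 = 16% of the planning effect. Varying the assumed conditions gives roughly 100 to 200 μm², that is 100/898 = 11% to 200/898 = 22%. Weaker dependence on the T1 value gives less, down to nothing.

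**The case against.** The best defence is that section 2.11 is a menu. A t test or regression on the change from T0 to T1 needs only those two biopsies and keeps a participant who skips T2. Nothing says the ANOVA is the sole or primary test, and imputation is not excluded. This stands in part. A reader might infer that the trial's main result will be confined to completers; the document does not say so, and the effect arises only if the ANOVA is used without imputation. Yet no listed method is tied to CSA, so nothing in the section protects the T1 comparison either.

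It can also be said that missing-data handling belongs in a statistical analysis plan that is not shown. Its absence is indeed no fault. The point rests on a method that is named and that is poorly matched to the stated principle.

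Two stronger readings are tempting and are not supported:

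- *That the trial expects about 25% drop-out.* The Discussion reports that about 75% completed a training program in an earlier study, cited for feasibility. Completing training is not the same as attending a biopsy, the figure says nothing about controls, and section 2.3 states no rate.
- *That the ANOVA could inflate the effect by some 40%.* That size arises if the quarter of the training arm with the smallest T0-to-T1 change is missing at T1: 0.424 × 840 = 356 μm², and 356/898 = 40%. But those T1 values are then unobserved under any method. A likelihood-based model using all T0 data would still be biased by about 276 to 335 μm² for T0–T1 correlations of 0.3 to 0.8. Most of that harm is neither caused by the ANOVA nor cured by replacing it.

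**Conclusion.** The concern holds in a limited, conditional form. Used without imputation, the named ANOVA discards valid T0 and T1 data from anyone missing T2, at odds with the intention-to-treat statement and in a trial that plans for drop-outs. The cost in power is small, about three percentage points in the example, and rests on assumed losses, d = 1.07 and a two-sided 5% level. Bias in the T1 comparison arises only if T2 loss is related to the T1 value and differs between arms; the 100 to 200 μm² is an illustration of that case, not a forecast. The change is worth making because a better-suited method is available at almost no cost, not because the trial is seriously compromised.

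**What to change.** In section 2.11, replace repeated-measures ANOVA for muscle fiber CSA with a linear mixed model for T0, T1 and T2. Specify group, time and group-by-time terms, an unstructured covariance matrix and small-sample degrees of freedom. State that it uses all available data from all randomised participants, and name the between-group contrast at T1 as the primary test, in line with hypothesis 2. The T2 contrast then comes from the same model.

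The cost is a change of wording and slightly more modelling work; no visit or measurement is added. The limitation should be stated alongside: the model corrects only for loss that can be predicted from observed data, so T1 biopsies lost for reasons related to their own unseen values remain a source of bias.

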### Randomization

2.4

After completion of baseline measurements, participants will be randomized by research staff in a 1:1 ratio to either the *intervention group* (supervised heavy-load RT during chemotherapy treatment) or to the *control group* (activity as usual during chemotherapy treatment), stratified on treatment (neo-adjuvant or adjuvant treatment). Sealed envelopes will be used to conceal the group allocation.

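### The stated comparison of muscle fiber CSA adjusts for neither its T0 value nor the randomisation stratum, which costs precision that could be had without new data

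*Protocol article*

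**What the plan says.** All references are to the protocol article.

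- Section 2.1: "The primary outcome for this study is muscle fiber size". Table 1 schedules CSA at T0, T1 and T2, so a baseline value is planned for every participant.
- Section 2.4: allocation is 1:1 and "stratified on treatment (neo-adjuvant or adjuvant treatment").
- Section 2.11: the methods listed are descriptive statistics, t tests, correlation, regression and "two-way repeated-measures ANOVA or the comparable nonparametric test as necessary to examine differences between and within groups" at the three time points. No model terms beyond group and time are given.
- Section 2.11, on covariates: "Should imbalances in important variables be detected, sensitivity analyses will also be added including these as covariates in the model". The article does not define which variables count as important or what counts as detecting an imbalance.
- Section 2.3: power rests on "a similar effect on muscle fiber size (+898 ± 840 μm^2"), and "50 participants (25 in each arm) will be recruited to account for drop-outs during the intervention".

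**The concern.** Two measurements that the design already provides, T0 CSA and the stratum, have no stated place as covariates in the main comparison. T0 does enter the repeated-measures ANOVA, but as one of the repeated responses. For a T0-T1 contrast that amounts to comparing change scores, which uses the baseline less efficiently than regressing on it.

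The stated covariate rule does not repair this. It selects variables by whether chance made the arms differ, not by whether the variable predicts CSA. Under randomisation, an observed imbalance is chance and says nothing about how much precision a covariate would add. Stratification also tends to keep the neo-adjuvant/adjuvant split close in the two arms, so the trigger would seldom pick the one factor that the design treats as important.

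At stake is precision in a biopsy study of 50 women. Validity is not at stake.

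**Working it through.** **Inputs.** Difference 898 μm² and SD 840 μm² (section 2.3), so d = 898/840 = 1.069. Per-arm sizes are 10, 16 and 25 (section 2.3). The article gives neither the test level nor its sidedness; two-sided 5% is assumed. It does not say whether 840 is an SD of change, of final values, or of one arm. It gives no T0-T1 correlation r; 0.3 to 0.9 is assumed.

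**The plan's own figures.** The article states "we need 10 participants in each group to get a statistical power of 80% in the present study" and "to further enhance the power up to 95%, we need 16 participants in each group". The usual formula is n = 2(z₁₋α/₂ + z_power)²/d², with d² = 1.143:

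- 80%: 2 × (1.960 + 0.842)²/1.143 = 13.7, so 14 (15 by noncentral t).
- 95%: 2 × (1.960 + 1.645)²/1.143 = 22.7, so 23 (24 by noncentral t).

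One-sided 5% by t gives 12 and 20. The stated 10 and 16 are therefore not reproduced with SD 840. They agree with each other at d of about 1.32 (SD about 680), so 840 may not be the SD that was used. The point made here does not depend on resolving this.

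**Variance ratios.** Let T0 and T1 have common variance σ² and correlation r.

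- Change score: Var = 2σ²(1 − r).
- Final value only: Var = σ².
- ANCOVA residual: Var = σ²(1 − r²).
- ANCOVA against change: (1 − r²)/[2(1 − r)] = (1 + r)/2.
- ANCOVA against a T1-only t test: 1 − r².

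**Power, reading 840 as the SD of change.** The noncentrality parameter is d√(n/2) with 2n − 2 df unadjusted, and d√(n/2)/√((1+r)/2) with 2n − 3 df for ANCOVA. Unadjusted, it is 3.02 at 16 per arm (power 83.3%) and 3.78 at 25 per arm (power 95.9%).

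| r (assumed) | (1+r)/2 | Power, 16 per arm | Power, 25 per arm |
|---|---|---|---|
| unadjusted | 1 | 83.3% | 95.9% |
| 0.3 | 0.65 | 95.2% | 99.6% |
| 0.5 | 0.75 | 92.1% | 99.0% |
| 0.7 | 0.85 | 88.7% | 98.0% |
| 0.9 | 0.95 | 85.0% | 96.7% |

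The ANCOVA rows ignore chance T0 differences between arms, which multiply the variance on average by about 1 + 1/(2n − 4): 1.036 at n = 16 and 1.022 at n = 25. With that factor, power at 16 per arm is about 94.5%, 91.2%, 87.6% and 83.8%, and at 25 per arm it falls by 0.3 points or less. At r = 0.9 the gain is then close to nil.

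**If the main test were a T1-only t test.** The ratio 1 − r² is 0.91, 0.75, 0.51 and 0.19 at r = 0.3, 0.5, 0.7 and 0.9. Reading 840 as the SD of final values, power at 16 per arm is 86.5%, 92.1%, 98.3% and above 99.9%, against 83.3% unadjusted.

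**Stratum.** Its prognostic strength is not given. For illustration only, suppose it explains 10% or 20% of the variance of the analysed quantity and the arms are balanced within strata. Omitting it inflates the standard error by 1/√(1 − 0.10) = 1.054 or 1/√(1 − 0.20) = 1.118. The nominal 5% test then runs at P(|Z| > 1.96 × 1.054) = 3.9% or P(|Z| > 1.96 × 1.118) = 2.8%.

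**The case against.** The strongest reply is that this is a short methods paragraph in a journal article, that its list of methods is open and includes regression, and that model terms usually sit in a statistical analysis plan. That stands against any complaint about silence alone. It does not answer the covariate rule that the article does state, which selects on the wrong criterion, nor the stratification whose factor has no stated role in the analysis.

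Several stronger readings may tempt a reader and should not be drawn:

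- **The primary model is chosen after seeing the data.** The imbalance sentence only adds sensitivity analyses; the main comparison does not change with observed imbalance. Even if such a trigger did govern the main test (ANCOVA if baseline p < 0.10, otherwise final values), simulation at 16 per arm gives a type I error of 1.8% to 4.2%, which is conservative.
- **Baseline is ignored.** T0 is one of the time points in the repeated-measures ANOVA.
- **The (1+r)/2 saving applies to the ANOVA as written.** With three occasions, the group-by-time test has two degrees of freedom. The ratio describes only a T0-T1 contrast.
- **Omitting the stratum invalidates the test.** If it is prognostic, omission errs on the conservative side. In a change analysis, a constant difference in CSA level between strata cancels, so the stratum would have to predict change to matter. Balance within strata is itself an assumption, because the article does not describe blocking.

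It is also fair to say that at 25 evaluable per arm the unadjusted power is already about 96% on these inputs, so the benefit matters mainly if drop-out is substantial or the effect is smaller than assumed.

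**Conclusion.** The point holds as a loss of efficiency, not as a validity error. The planned unadjusted comparison of randomised arms is sound. Adjusting for T0 CSA would reduce the variance of a T0-T1 change comparison by 5% to 35% (r from 0.9 down to 0.3). At 16 per arm that is worth roughly 2 to 12 points of power, about one point less once chance baseline differences are counted. At 25 per arm it is worth roughly 1 to 4 points. These figures rest on an assumed r, on equal variances at T0 and T1, on 840 being the SD of change, and on a two-sided 5% test. Against a T1-only t test the gain follows 1 − r² and grows with r. The benefit of adding the stratum cannot be quantified from the document.

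The imbalance rule is a weakness of the sensitivity analyses only: it is undefined and selects covariates by chance difference instead of prognostic value.

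**What to change.** State in section 2.11 that the primary comparison regresses T1 CSA on group, T0 CSA and the neo-adjuvant/adjuvant stratum. An equivalent is a baseline-adjusted mixed model with the same terms that also includes T2. Replace the imbalance trigger with a short list of sensitivity-analysis covariates, named in advance because they are expected to predict CSA.

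The cost is a sentence or two of text and about two degrees of freedom (one for T0 CSA, one for the stratum). No new measurements or participants are needed, because T0 CSA and the stratum are already collected.
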